### 1224 **5.5.2 Sample size and power calculations**

1225 To assess the appropriate study sample size and compute study power, we used a carefully designed  
1226 computer simulation allowing for 20% dropout by both sites and patients. Drawing on data from  
1227 1,612 consecutive patients (59), outcome data were generated to mimic pain scores we expect to see  
1228 in the presenting population. We generated data from a beta distribution (scaled 0 to 1), rescaled to  
1229 lie between 0 and 10, then rounded to integer values. We then discarded patients with scores of  $< 2$   
1230 to represent the sample of interest. We allowed centre-specific means to vary between .05 and .15 to  
1231 generate an appropriate intra-class correlation. We used a standard minimally important difference  
1232 of .5 effect size (60). To more closely represent reality, we allowed for variation in the responses of  
1233 each patient to intervention. Once a hypothetical study population had been generated, we ran a  
1234 linear mixed model that included an intervention effect as well as an intervention by time effect, as  
1235 well as a random centre effect. We repeated this whole process several hundred times and then  
1236 estimated power by computing the proportion of times that the null hypothesis would be rejected.  
1237 We did this both for the main intervention effect, as well as the intervention by time effect. Two-  
1238 sided hypothesis tests with type I errors of 0.05 were used. Assuming 82 patients per centre at 6  
1239 sites ( $N=492$ ), our study will have  $>90\%$  power to detect the main effect. The study will oversample  
1240 by 2 sites (i.e. a total of 8 sites) and 18 patients per site (i.e.  $N=100$  at each site) to allow for drop-  
1241 out.

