### **Intervention arm**

During a training phase, designated 'champions' and staff at each centre will attend workshops to learn about the project and how to tailor implementation strategies to their centre's needs. Implementation strategies will include:

1. An audit tool to enable centres to monitor how well they are implementing core standards of cancer pain assessment and management;
2. Tools for identifying barriers and facilitators to cancer pain screening, assessment and management and strategies to overcome barriers;
3. QStream online health professional education to test and consolidate knowledge of cancer pain assessment and management;
4. Patient-held resources to ensure management remains centred on individual patient needs, support patient-health professional communication and coordination and help patients advocate for evidence-based, person-centred care;

In the intervention phase, implementation strategies will be put in place and monitored. A community of practice between staff at different centres implementing the strategies will be facilitated by means of regular teleconferences, chaired by a project team member.

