## 1209 **5.5 STATISTICS**

### 1210 **5.5.1 Statistical analysis**

1211 For the main analysis, linear mixed models (5) will be used to model the outcomes of interest, while  
1212 accounting for the clustering and longitudinal design. Although designed for the analysis of  
1213 continuous outcomes, we have conducted computer simulations to confirm that this approach will  
1214 work very well for the pain and other NRS scores that are measured on a ten point scale. The linear  
1215 mixed modeling framework is very flexible. For example, it will allow for testing whether treatment  
1216 effects diminish over time. It will also allow the incorporate of additional covariates of interest, for  
1217 instance patient age, gender, ethnicity and other factors related to their type of disease; and  
1218 inclusion of covariates that reflect characteristics of the study centres. Statistical analysis will be  
1219 performed using the library lme4 in the R package (58). Analyses will be repeated for all patients  
1220 and patients newly referred during the intervention arm to control for the possibility that outcomes  
1221 are influenced by care received prior to the intervention being implemented. For secondary patient  
1222 outcomes, analyses will be repeated for patients with clinically significant ( $\geq 2$ ) and moderate-severe  
1223 ( $\geq 5$ ) worst and average pain.

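### The >90% power and 0.05 level in Section 5.5.2 rest on one random centre intercept and no centre-level variation in effect, although the intervention is tailored centre by centre

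*Protocol*

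**What the plan says.** Section 5.5.2 describes the only model that the protocol spells out. Centre means are allowed to differ so as to create an intra-class correlation. Heterogeneity of response is then added for patients: the target is a standardised difference "of .5 effect size (60). To more closely represent reality, we allowed for variation in the responses of" each patient. The fitted model contains the intervention, intervention by time, "well as a random centre effect. We repeated this whole process several hundred times and then" power was estimated from the share of rejections. On the error level: two-"sided hypothesis tests with type I errors of 0.05 were used". With 82 patients at each of 6 sites the result is >90% "power to detect the main effect. The study will oversample" to 8 sites and 100 patients per site.

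Section 5.5.1 says that linear mixed models will account for the clustering and the longitudinal design, with analysis "performed using the library lme4 in the R package". It neither lists the random effects nor limits them to a centre intercept.

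On the intervention, the Trial Summary (Intervention arm) has champions and staff attend workshops to "learn about the project and how to tailor implementation strategies" to their own centre. Section 4.1.2 gives champions on-site training to adapt the package locally and lets their division of tasks differ by site. Section 1.3 calls the package a complex intervention whose components interact with contextual factors.

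**The concern.** A random centre intercept absorbs differences between centres in their general pain level. It does not absorb differences in how much the intervention achieves, or shifts in a centre's level from one period to the next. Each centre acts as its own control (Section 3.6), so the estimate leans heavily on within-centre contrasts. If those contrasts truly differ between centres, their average is known only as precisely as 6 to 8 centres allow. The intercept-only model treats that variation as patient noise and credits the estimate with the precision of several hundred patients.

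The simulation added patient-level variation for the sake of realism but left out the level at which the package is delivered and adapted. At stake are the stated power, the stated 5% level and, if the same model is used for the trial data, the width of the confidence intervals.

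**Working it through.** **Inputs from the protocol.** Two-sided 0.05; effect 0.5 SD; 82 patients × 6 centres = 492 for the power statement; 100 × 8 = 800 as the recruitment target; half of each centre's patients in each arm (Trial Summary, Sample size).

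**Assumed, because the protocol gives no value.** Total patient SD 1; ICC 0.05; between-centre SD of the effect τ from 0.10 to 0.20 SD (0.25 as a further case); cluster autocorrelation 0.8. For the runs with period effects, one centre crosses per step, with each centre's patients spread evenly over its control periods and over its intervention periods. The outcome is continuous, as in the protocol's simulation. The intervention-by-time term is left out.

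**1. The plan's own figure.** With 246 per arm, SE = √(2/246) = 0.0902. Power = Φ(0.5/0.0902 − 1.96) = Φ(3.59) = 0.9998. The bound of >90% is consistent with its stated inputs. The beta parameters, ICC and step schedule are not given, so only the bound can be checked.

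**2. Effect variation between centres, no period effects.** The estimate is the mean of K within-centre differences.

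- Model variance: 4(1 − ICC)/N
- True variance: 4(1 − ICC)/N + τ²/K
- Actual level: 2[1 − Φ(1.96 × SE_model/SE_true)]

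For 8 × 100, the model variance is 4 × 0.95/800 = 0.00475, so SE_model = 0.069.

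- τ = 0.10: true variance 0.00475 + 0.00125 = 0.00600, SE_true 0.077, level 8.1%
- τ = 0.20: true variance 0.00475 + 0.00500 = 0.00975, SE_true 0.099, level 17.1%

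**3. The same with period effects.** The formula for the level is unchanged. SE_true is the sandwich variance of the random-intercept generalised least squares estimator.

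| Design | τ | Level, no period effects | Level, period effects |
|---|---|---|---|
| 6 × 82 | 0 | 5.0% | 5.0% |
| 6 × 82 | 0.10 | 7.5% | 5.8% |
| 6 × 82 | 0.20 | 15.1% | 8.2% |
| 6 × 82 | 0.25 | 20.1% | 10.0% |
| 8 × 100 | 0 | 5.0% | 5.0% |
| 8 × 100 | 0.10 | 8.1% | 6.0% |
| 8 × 100 | 0.20 | 17.1% | 9.0% |
| 8 × 100 | 0.25 | 22.8% | 11.2% |

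For 8 × 100 with period effects, SE_model is 0.124 and SE_true is 0.130 at τ = 0.10 and 0.144 at τ = 0.20. Simulation of 20,000 trials per setting (balanced design, no period effects) agrees. At τ = 0 it gives 4.9% with 6 centres and 5.1% with 8.

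**4. Centre-by-period variation.** ICC 0.05 with autocorrelation 0.8 corresponds to a period-specific variance of about 0.05 × (1 − 0.8) = 0.01, an SD of 0.10. For 8 × 100 the level is 6.2% with period effects (SE 0.124 against 0.130) and 7.1% without (0.069 against 0.075).

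**5. With the extra term fitted.** A centre-by-intervention effect tested on t with K − 1 degrees of freedom held 4.8–5.1% in the simulations. Power without period effects, at τ = 0.10 / 0.20 / 0.25, was 0.98 / 0.91 / 0.84 for 6 × 82 and 1.00 / 0.99 / 0.97 for 8 × 100. Once this term is in the model the degrees of freedom matter: using 1.96 gives 2P(t₇ > 1.96) = 9.1% and 2P(t₅ > 1.96) = 10.7%.

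**The case against.** The sentence at issue describes a model fitted to generated data for sample size. The analysis section calls the mixed-model framework flexible, and lme4 can fit a centre-by-intervention term. The random-effect structure and the degrees-of-freedom method may properly sit in a statistical analysis plan that is not at hand. A reader might infer that the trial's confidence intervals will be too narrow. The protocol does not support that: Section 5.5.1 commits to no intercept-only model and mentions no large-sample z-test. This part of the objection stands.

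A reader might also infer that 6 to 8 centres are enough by themselves to break the 5% level. They are not: at τ = 0 the level is 5.0%. The 9% and 11% figures arise only after the centre-by-intervention term is fitted and the normal reference is kept.

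Further, tailoring makes variation in effect plausible but does not prove it. If the package did nothing at any centre, τ would be zero. The inflation from τ describes a mean effect of zero with centres truly differing around it. Only centre-by-period variation survives a null of no effect anywhere, and at autocorrelation 0.8 that costs one to two percentage points.

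Lastly, power without period effects stays above 90% for 6 × 82 up to τ = 0.20. Modelling calendar time alone lowers it to 0.876 at τ = 0, but that is a separate issue.

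What the objection does not remove is Section 5.5.2 itself. Its power and error level are stated as results, and they come from data and a model without the centre-level variation that the protocol's account of the intervention leads one to expect.

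**Conclusion.** The point holds as a conditional one. The stated power and 5% level in Section 5.5.2 assume that the effect is the same at every centre and that centre levels are stable over periods. Sections 1.3 and 4.1.2 give reason to doubt the first, and nothing in the protocol supports the second. If the same model is used for the trial data and either assumption fails, the standard error is too small.

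For 8 × 100, ICC 0.05 and an assumed τ of 0.10 to 0.20 SD, the true standard error is 1.04 to 1.16 times the model's with period effects (level about 6–9%) and 1.12 to 1.43 times without (about 8–17%). Autocorrelation of 0.8 gives about 6–7%. All of these rest on assumed centre-level variances and, where periods are modelled, on an assumed step schedule. The figures are on a continuous scale, so for the binary primary endpoint they indicate order of magnitude only. This is worth correcting; it does not show that the planned analysis is invalid.

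**What to change.** - State the random-effect structure for the primary and secondary models: a centre intercept plus a random centre-by-intervention and/or centre-by-period effect, with a small-sample degrees-of-freedom correction (Kenward-Roger for the linear models).
- Confirm the primary result with a permutation test over the randomised crossover order. This is valid for the null of no effect at any centre and does not depend on the variance model.
- Rerun the Section 5.5.2 simulation with centre-level variation in the effect and in period levels, over a range of SDs (for example 0 to 0.30 SD for the effect). Report the ICC used, and restate both power and type I error.

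The cost is some wording and computing, somewhat wider intervals and a lower stated power. No change to recruitment or conduct follows from this point alone. The power lost to calendar-time effects should be dealt with separately, so that the two are not confused in the restated figures.

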### 1242 **5.5.3 Cost-effectiveness analysis**

1243 The primary outcome for cost-effectiveness analysis will be the incremental cost per additional  
1244 responder at the end of Week 1 (response is defined as a clinically important improvement of 30%  
1245 on a 0-10 NRS 1 week post-screening for those with moderate-severe ( $\geq 5$ ) worst pain). Quality of  
1246 life data collected at weeks 1, 2 and 4 will be used to conduct a modelled cost-utility analysis. As  
1247 economic data may be skewed, confidence intervals will be estimated with bootstrap methods (6).  
1248 Sensitivity analysis will examine the effect of assumptions and determine which cost components  
1249 drive the results.

#### 1250 **5.5.4 Qualitative analysis**

1251 Thematic coding and classifying techniques will underpin the analysis of semi-structured interviews  
1252 and focus groups (7).

### 1253 **6.0 ETHICS**

#### 1254 ***6.1 Benefit anticipated from the study***

1255 The proposed project aims to test cost-effectiveness of an intervention with potential to enable  
1256 equitable care for people with cancer pain across Australia. Currently, patients are subjected to a  
1257 ‘lottery’ regarding quality of care, especially in regional and rural areas. While this is partly due to  
1258 lack of specialist services, research suggests that even the basics of pain assessment and  
1259 management are often not offered, despite making limited requirements on resources. The  
1260 guidelines to be implemented in this project include recommendations and processes to ensure  
1261 minimum standards of pain assessment and management can be achieved regardless of the  
1262 availability of specialist services. Another key to the problem is empowering patients and carers to  
1263 self-manage pain and take the lead in coordinating their care with appropriate resources and  
1264 support. The implementation package to be tested in the proposed project includes a patient-held  
1265 resource to help patients advocate for person-centred, evidence-based care.

1266  
1267 Subgroups of people with advanced breast and other cancers who stand to benefit  
1268 disproportionately from intervention are patients with limited English and health literacy. Australian  
1269 research suggests cancer patients from non-English speaking backgrounds may have greater unmet  
1270 needs arising from problems with communicating with health professionals and lack of knowledge  
1271 of the health system. In the proposed project, tools for pain screening and patient-held resources  
1272 will be translated into community languages to ensure that medical teams are made aware when  
1273 patients have pain without relying on verbal communication. Patient-held resources have been  
1274 developed for a basic level of literacy and are intended to empower patients to manage their pain  
1275 and support discussion with medical teams regarding pain management plans and who to contact for  
1276 support under different circumstances.

#### 1277 ***6.2 The possibility of psychological stress***

1278 Some participants may experience stress associated with recounting their experiences when  
1279 completing interviews for the qualitative sub-study of this project. This is a vulnerable population,  
1280 where sensitive issues about ability to function and other questions may raise broader issues of  
1281 psychological distress.

1282  
1283 Participants who take part in interviews will have chosen to do this as an ‘optional extra’ in addition  
1284 to participation in the rest of the project. There will be no deception of participants at any stage.  
1285 Each participant interaction will be undertaken by carefully selected and trained study staff. This  
1286 training will initially be undertaken in conjunction with investigators and senior research personnel,  
1287 who have been trained in Good Clinical Practice, to ensure that staff are able to detect and monitor  
1288 participant distress.

1289  
1290 Although there may be acute distress, the weight of evidence is that such ‘prompt’ questions are in  
1291 fact an avenue to open up discussions which are well regarded by people despite their initial  
1292 potential distress.

### **6.3 Research on people in dependent relationships**

The nature of doctor-participant relationships dictates that patient and carer participants may feel that they are in the dependent position. The investigators and their designees will work to minimise any concern of inappropriate influence—the presentation of the study will be as unbiased as possible, the information sheet and consent forms will be clear, and participants will be able to withdraw from the study at any time. A person not directly involved in the clinical care of the participant will collect primary outcome data and obtain consent to provide data for secondary outcomes. Research assistants undertaking informed consent will be trained to identify their roles as research-only and to present the study in such a way that clinical care is separated. Training will provide an opportunity for project staff to determine appropriate ways of dealing with clinical situations that might arise during their research visits. Patient participants will be cared for as individuals with specific needs; the needs of research will come second.

Where patients report pain of NRS 2+ to research staff at follow-up, research staff will provide them with contact details for their medical team and invite them to call for assistance. It is not the research staff's role to provide clinical care to patients.

### **6.4 Method and nature of recruitment and advertising**

Participants will be recruited following initial screening in the participating clinics at each site. Any participant who is approached to take part in this study has the right of refusal. Refusal to take part in this study will not adversely affect the provision or quality of care provided to any participant in any way.

### **6.5 Protection of privacy and preservation of confidentiality**

All participants will be allocated a unique ID number. The master list linking identifying participant information and ID number will be maintained in a locked cabinet, separate from the participant database. Form tracking will be via participant ID number only. There will be master lists held at each participating site and at the coordinating site. The participant database will be stored on a password-protected hard drive maintained by the study investigators. Data will be analysed by ID number only.

Data relating to the primary outcome (screening, cancer and other diagnoses, age, gender and language spoken at home) will be de-identified before leaving each centre for those patients who do not consent to take part in secondary outcome assessments.

### **6.6 Restriction of use of data**

Investigators will have access to data by ID number only for the purposes of data monitoring and analysis. The Project Coordinator will have access to all study data for the purposes of data checking, monitoring and preparation for analysis. Study research assistants and site investigators will have access to the local site consent forms, Case Report Forms and the data contained within for the purposes of data collection, data entry and data query resolution. Study auditors will have access to Case Report Forms (by ID number only) and study files in order to audit the study. Site research ethics committees will have access to local data for audit purposes.

### **6.7 Use of personal information**

Only enough personal information to give a general demographic and disease profile of the participant will be collected, along with details needed to enable contact via post and telephone. Data on language spoken at home will be collected because of the hypothesis that patients who are

1337 less proficient in English will benefit especially from the intervention. The participant responses  
1338 collected are limited to those that will address the study’s primary and secondary aims.

1339 **6.8 Estimated time of retention of personal information and**  
1340 **planned disposal**

1341 Records from the study will be maintained for 15 years after study completion in secure archiving  
1342 facilities. Once the 15 year waiting period is complete, the files will be erased from the database  
1343 hard-drive and any paper copies shredded, including the master list linking participant name and  
1344 treatment number.

1345  
1346 The data will be retained in accordance with good clinical practice recommended by the NHMRC  
1347 National Statement and the GCP guidelines, and in a form that is at least as secure as the sources  
1348 from which it was obtained.  
1349

1350 **7.0 STUDY ADMINISTRATION**

1351 **7.1 Data handling and record keeping**

1352 **7.1.1 Direct access to source data**

1353 A statement of permission to access source data for regulatory and audit purposes will be included  
1354 within the PISCF with explicit explanation about this given as part of the consent process.  
1355 Specifically, access will be required by study staff (including investigators, site coordinators and  
1356 study nurses), Hospital Research Ethics Committees (HRECs) and the data management team. In  
1357 addition, de-identified data will be made available for meta-analysis and where requested by  
1358 journals for publication purposes.

1359  
1360 Case Report Forms (CRFs) for patients and carers will include:

- 1361
- 1362 • CRF – Patient Primary Data (week 1)
  - 1363 • CRF – Patient Secondary Data (weeks 1, 2, 4)
  - 1364 • CRF – Carer Data (weeks 2, 4)

1365 **7.1.2 Data collection**

1366 Data will be sourced from the following.

| Measure                                  | Source               | Completed by:                                        |
|------------------------------------------|----------------------|------------------------------------------------------|
| Efficacy on patient pain                 | Screening data / CRF | Automated / research assistant / local trials nurses |
| Efficacy on patient QOL                  | CRF                  | Automated / research assistant/ local trials nurses  |
| Efficacy on patient empowerment          | CRF                  | Research assistant/ local trials nurses              |
| Performance status                       | Medical records      | Research assistant/ local trials nurses              |
| Efficacy on carer experience             | CRF                  | Research assistant/ local trials nurses              |
| Resource utilization (individual)        | MBS/PBS data         | Research assistant/ local trials nurses              |
| Semi-structured interview / focus groups | Recordings           | Research assistant                                   |

|                                            |               |                                         |
|--------------------------------------------|---------------|-----------------------------------------|
| Structural data – centre level             | Audit         | Research assistant/ local trials nurses |
| Structural data – staff level (staff time) | Online survey | Centre staff                            |
| Process data – patient level               | Audit         | Research assistant/ local trials nurses |
| Process data – centre level                | Audit         | Centre staff                            |

